| STUDY SCHEDULE     | 
There will be a Screening window that is up to 30 days where all necessary assessments will be conducted to determine eligibility prior to randomization on study Day 1. Investigational product (test article) administration will occur on Day 1 for each randomized subject and will be given by an unblinded administrator.
 
In-clinic safety evaluations will be performed at screening, at Day 1 before and after administration of the test articles, and at Days 2 (+1), 4 (<math>\pm 1</math>), 8 (<math>\pm 2</math>), 15 (<math>\pm 2</math>), 29 (<math>\pm 2</math>), 57 (<math>\pm 2</math>), 85 (<math>\pm 7</math>), 119 (<math>\pm 7</math>) and 180 (<math>\pm 7</math>).
 
Telephone calls from the site to the participant will be made on Days 5, 6 and 7.
 
Photographs of the MIMIX MAP application site will be taken on the day of administration (pre-dose, then 1 (<math>\pm 2</math>), 30 (<math>\pm 5</math>) and 60 (<math>\pm 5</math>) minutes post-MAP removal), and on Days 2 (+1), 4 (<math>\pm 1</math>), 8 (<math>\pm 2</math>), 15 (<math>\pm 2</math>), 29 (<math>\pm 2</math>), 57 (<math>\pm 2</math>) and 180 (<math>\pm 7</math>).
 
Specimens for assessment of immune response will be collected at screening, before first vaccination on Day 1, and on Days 29 (<math>\pm 2</math>), 57 (<math>\pm 2</math>), 85 (<math>\pm 7</math>), 119 (<math>\pm 7</math>) and 180 (<math>\pm 7</math>).
 
A detailed schedule of assessments appears in Table 5.
                                                                                                                                                                                                                                                                              |

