| SAFETY ASSESSMENTS | 
On day of vaccination, observe study participants in clinic for a minimum of 1 hour (+ 30 minutes) post-dose as directed by the study physician or designate.
 
Solicitation of local and systemic reactogenicity events will be captured via clinic visits as applicable using standardized grading. Reactogenicity assessment will also include unsolicited complaints.
 
All local and systemic reactogenicity reporting in the 7 days after immunization will be supported via in-person visits and telephonically. Calls are to query for any adverse events using, complete Appendix 1, 2 and the systemic section of Appendix 3, and to determine if an on-site visit is needed.
 
Skin tolerability assessments including pain, induration, tenderness, erythema and edema (Appendix 1: Local Tolerability Scoring) will be carried out on the day of administration (pre-dose, then 1 (<math>\pm 2</math>), 30 (<math>\pm 5</math>) and 60 (<math>\pm 5</math>) minutes post-MAP removal), and on Days 2 (+1), 4 (+1), 8 (<math>\pm 2</math>). Erythema assessments only will be carried out on Days 15 (<math>\pm 2</math>), 29 (<math>\pm 2</math>), 57 (<math>\pm 2</math>) and 180 (<math>\pm 7</math>).
 
Other local tolerability assessments of the MAP application site including bruising, itching, skin flaking and pigmented skin coloration (Appendix 2: Other Local Tolerability Scoring) will be carried out on the day of administration (pre-dose and 60 (<math>\pm 5</math>) minutes post-MAP removal), and on Days 2 (+1), 4 (<math>\pm 1</math>), 8 (<math>\pm 2</math>). Pigmented coloration assessments only will be carried out on Days 15 (<math>\pm 2</math>), 29 (<math>\pm 2</math>), 57 (<math>\pm 7</math>) and 180 (<math>\pm 7</math>).
 |

|                                   |                                                                                                                                                                                                                                                                                                                                                                                                                                           |                               |

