On Day 2 (24 hr post treatment), participants will return to the clinic for an abbreviated physical exam, vital sign measurements, a review of any systemic or local site reactions (skin tolerability and other local tolerability assessments) and for further application site photographs to be taken.

On Day 4 (3 days post treatment), participants will return to the clinic for an abbreviated physical exam, vital sign measurements, a review of any systemic or local site reactions (skin tolerability and other local tolerability assessments) and for further application site photographs to be taken. Blood samples will be collected for hematology and chemistry.

On Day 5, 6 and 7 a phone call will be made to participants to ask about spontaneous adverse events or changes on concurrent medication.

On Day 8 ( $\pm 1$  day) participants will return to the clinic for an abbreviated physical exam, vital sign measurements, a review of any systemic or local site reactions (skin tolerability and other local tolerability assessments) and for further application site photographs to be taken.

On Day 15 (+/- 2 day), participants will return to the clinic for an abbreviated physical exam, vital sign measurements, for erythema ([Appendix 1: Local Tolerability Scoring](#)) only and pigmented coloration assessments ([Appendix 2: Other Local Tolerability Scoring](#)) only and for further application site photographs to be taken.

On Day 29 (+/- 2 day) participants will return to the clinic for an abbreviated physical exam, vital sign measurements, for erythema ([Appendix 1: Local Tolerability Scoring](#)) only and pigmented coloration assessments ([Appendix 2: Other Local Tolerability Scoring](#)) only and for further application site photographs to be taken. Blood samples will be collected for hematology, biochemistry and immunogenicity analysis.

On Day 57 (+/- 4 days), participants will return to the clinic for additional application site photographs, an abbreviated physical exam, vital sign measurements and for erythema ([Appendix 1: Local Tolerability Scoring](#)) only and pigmented coloration assessments ([Appendix 2: Other Local Tolerability Scoring](#)) only. Blood samples will be collected for immunogenicity analysis.

On Day 85 (+/- 7 days), participants will return to the clinic for an abbreviated physical exam and vital sign measurements. Blood samples will be collected for immunogenicity analysis.

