- l. All photographs should be taken with the study specific iPhone or the study specific DermLite DL4 Dermatoscope attached to the iPhone. Subject ID, Subject initials, and timepoint should be included in each iPhone photograph with a label. On Study Day 1, iPhone photographs should be taken of the treatment site both pre dosing (within 30 minutes prior to dosing) and 1 + 2 minutes, 30 ± 5 and 60 ± 5 minutes post removal of the MAP. iPhone photographs will also be taken a single time on Days 2, 4, 8, 15, 29, 57 and 180. For each iPhone photograph hold the phone 8-10 cm above the Application site, take one, in focus, 1x magnification photo. Capture the Application site and label.
- Dermatoscope images will be taken with the Dermatoscope attached to the iPhone, the lens spacer rotated to '0' and the faceplate removed. The image will be taken with the lens spacer gently touching the application site periphery. The rim of the Dermatoscope lens spacer should be wiped with alcohol before and after use. Photographs with the Dermatoscope attached to the iPhone should be taken of the treatment site pre dosing (within 30 minutes prior to dosing) and a single time on Days 29 and 180. Photographs with the Dermatoscope should be 'captioned' using the iPhone 'add a caption' function. The Caption should include the Subject ID, initials and timepoint. All photos should be taken under consistent lighting conditions. All photographs will be uploaded to a secure file system, BOX. Please see VX-103-01 Imaging Instructions for additional instructions.
- m. Standard adverse event collection will take place from the time the informed consent is signed through Day 29. This will capture all adverse events that are not included from the solicited adverse event collection appendices.
- n. These calls are to query for any adverse events, complete Appendix 1, 2 and the systemic section of Appendix 3 and determine if an on-site visit is needed.

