#### 9.1.4 Study stopping rules

| Event                                                                          | Number of Participants |
|--------------------------------------------------------------------------------|------------------------|
| Death or any life-threatening SAE                                              | 1                      |
| Any SAE that cannot reasonably be attributed to a cause other than vaccination | 1                      |
| Any withdrawal from the study or withdrawal from study                         | 1                      |

|                                                                                                                                                                                                                                                                                                                                                                                                                                     |   |
|-------------------------------------------------------------------------------------------------------------------------------------------------------------------------------------------------------------------------------------------------------------------------------------------------------------------------------------------------------------------------------------------------------------------------------------|---|
| vaccine(s)/product(s) (by investigator or subject request) following a grade 3 AE that cannot reasonably be attributed to a cause other than vaccination                                                                                                                                                                                                                                                                            |   |
| Any local or general solicited AE leading to hospitalization, or fever > 40°C or 104°F (oral route) that cannot reasonably be attributed to a cause other than vaccination, or necrosis at the injection site, within the 7-day (Days 1-7) post-vaccination period                                                                                                                                                                  | 1 |

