## APPENDICES

### Appendix 1: Local Tolerability Scoring

Local tolerability scoring is adapted from the 2007 Food and Drug Association (FDA) Healthy Adult and Adolescent Volunteers Enrolled in Preventive Vaccine Clinical Trials (FDA, 2007) for assessment of Vaxess's 1 cm square MAP .

| Local Reaction to Product | Grade 0                | Mild (Grade 1)                                | Moderate (Grade 2)                                                                | Severe (Grade 3)                                             | Potentially Life Threatening (Grade 4)       |
|---------------------------|------------------------|-----------------------------------------------|-----------------------------------------------------------------------------------|--------------------------------------------------------------|----------------------------------------------|
| Pain                      | Pain is absent         | Does not interfere with activity              | Repeated use of non-narcotic pain reliever > 24 hours or interferes with activity | Any use of narcotic pain reliever or prevents daily activity | Emergency room (ER) visit or hospitalization |
| Tenderness                | No discomfort to touch | Mild discomfort to touch                      | Discomfort with movement                                                          | Significant discomfort at rest                               | ER visit or hospitalization                  |
| Erythema/Redness*         | <1 cm                  | 1– 5 cm                                       | 5.1 – 10 cm                                                                       | > 10 cm                                                      | Necrosis or exfoliative dermatitis           |
| Induration/ Swelling **   | <1 cm                  | 1 – 5 cm and does not interfere with activity | 5.1 – 10 cm or interferes with activity                                           | > 10 cm or prevents daily activity                           | Necrosis                                     |

\*In addition to grading the measured local reaction at the greatest single diameter, the measurement should be recorded as a continuous variable.

\*\* Induration/Swelling should be evaluated and graded using the functional scale as well as the actual measurement.

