#### Clinical Abnormalities:

| Vital Signs *                         | Mild (Grade 1)               | Moderate (Grade 2)           | Severe (Grade 3)         | Potentially Life Threatening (Grade 4)                 |
|---------------------------------------|------------------------------|------------------------------|--------------------------|--------------------------------------------------------|
| Fever (°C) **
(°F) **              | 38.0 – 38.4
100.4 – 101.1 | 38.5 – 38.9
101.2 – 102.0 | 39.0 – 40
102.1 – 104 | > 40
> 104                                          |
| Tachycardia - beats per minute        | 101 – 115                    | 116 – 130                    | > 130                    | ER visit or hospitalization for arrhythmia             |
| Bradycardia - beats per minute***     | 50 – 54                      | 45 – 49                      | < 45                     | ER visit or hospitalization for arrhythmia             |
| Hypertension (systolic) - mm Hg       | 141 – 150                    | 151 – 155                    | > 155                    | ER visit or hospitalization for malignant hypertension |
| Hypertension (diastolic) - mm Hg      | 91 – 95                      | 96 – 100                     | > 100                    | ER visit or hospitalization for malignant hypertension |
| Hypotension (systolic) – mm Hg        | 85 – 89                      | 80 – 84                      | < 80                     | ER visit or hospitalization for hypotensive shock      |
| Respiratory Rate – breaths per minute | 17 – 20                      | 21 – 25                      | > 25                     | Intubation                                             |

\* Subject should be at rest for all vital sign measurements.

\*\* Oral temperature; no recent hot or cold beverages or smoking.

\*\*\* When resting heart rate is between 60 – 100 beats per minute. Use clinical judgement when characterizing bradycardia among some healthy subject populations, for example, conditioned athletes.

| Systemic (General) | Mild (Grade 1)                                           | Moderate (Grade 2)                                                                       | Severe (Grade 3)                                                                 | Potentially Life Threatening (Grade 4)            |

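### As written, the Day 5–7 calls do not solicit fever, and no method is given for obtaining temperature or lesion diameter between visits, although the Days 1–7 halting rules use both

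*Protocol*

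**What the plan says.** The protocol describes the Day 5–7 calls in several places, and the descriptions differ.

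- **Timing.** The synopsis (Study Schedule) states: "Telephone calls from the site to the participant will be made on Days 5, 6 and 7".
- **Table 5, footnote n (Section 8).** "These calls are to query for any adverse events, complete Appendix 1, 2 and the systemic section of Appendix 3". The same sentence has the caller "determine if an on-site visit is needed".
- **Synopsis, Safety Assessments.** Staff are to "complete Appendix 1, 2 and the systemic section of Appendix 3, and to determine if an on-site visit is needed".
- **Section 3.** On the same days, "a phone call will be made to participants to ask about spontaneous adverse events or changes on concurrent medication". No appendix is mentioned.
- **Synopsis, Study Design.** Telephone contact is promised on any day without an in-person visit through 8 days after treatment, with assessment of solicited systemic and local reactions.

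Appendix 3 divides its clinical part into two tables. Fever is in Vital Signs, with the note "Oral temperature; no recent hot or cold beverages or smoking". The Systemic (General) table holds nausea/vomiting, diarrhea, headache, fatigue and myalgia.

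Appendix 1 grades erythema and induration by centimetre cut-offs, and for erythema it adds: "In addition to grading the measured local reaction at the greatest single diameter, the measurement should be recorded as a continuous variable". Appendix 2 grades bruising in centimetres.

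Section 9.1.4 and the synopsis halt the study for one participant with "fever > 40°C or 104°F (oral route) that cannot reasonably be attributed to a cause other than vaccination" in the Days 1–7 window. They also list grade 3 solicited local and general events lasting 48 hours or more in the same window.

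**The concern.** Fever has its own row in the grading scale and is a named halting trigger, but the call instruction points to the one clinical table in Appendix 3 that leaves it out. A site that follows footnote n to the letter has no prompt to ask about fever on Days 5, 6 or 7. Even if a participant mentions one, the protocol does not say where a temperature reading would come from. The size-based local scores have a similar problem. The calls must complete Appendices 1 and 2, yet nothing says how a diameter is obtained over the telephone.

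Reactogenicity is part of the primary endpoint (Section 12.4.1) in a first-in-human study with 15 participants per arm. One unrecorded fever is 1/15 = 6.7% of an arm. A temperature that was never taken cannot be restored at the analysis stage.

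**Working it through.** The protocol gives no figure to reproduce. The check compares texts and counts days.

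**Step 1: what the calls cover.**

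| Item | Where it is graded | Covered by footnote n as written? | Can be graded by phone without measuring? |
|---|---|---|---|
| Fever | Appendix 3, Vital Signs | No | No |
| Nausea/vomiting, diarrhea, headache, fatigue, myalgia | Appendix 3, Systemic (General) | Yes | Largely |
| Pain, tenderness | Appendix 1 | Yes | Yes |
| Induration, functional part | Appendix 1 | Yes | Yes |
| Erythema; induration size | Appendix 1, cuts at 1, 5 and 10 cm | Yes | No |
| Bruising | Appendix 2, cuts at 2 and 5 cm | Yes | No |
| Itching, skin flaking | Appendix 2 | Yes | Yes |

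Under Section 3, none of these rows is solicited on Days 5–7.

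**Step 2: scheduled measurement in the halting window.** Temperature is one of the vital signs (Table 5, footnote g), which are taken at clinic visits. On nominal days:

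- Days with a visit: 1, 2 and 4, so 3 of 7.
- Days without one: 3, 5, 6 and 7, so 7 − 3 = 4 of 7 (57%).
- Of those four, Days 5, 6 and 7 have a call. Day 3 has neither a visit nor a listed call, despite the promise in the synopsis.

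**Step 3: visit windows.** The Day 8 window is ±2 days in the synopsis and ±1 day in Section 3. An early Day 8 visit can fall on Day 6 or 7 under the synopsis, or on Day 7 under Section 3. At most 3 + 1 = 4 of the 7 days then have a scheduled measurement.

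**Step 4: interval against the duration criterion.** Nominally, the gap from the Day 4 to the Day 8 visit is 8 − 4 = 4 days = 96 hours, which is 96/48 = 2 times the 48-hour criterion. A grade 3 episode can therefore start, last long enough to qualify and resolve between two scheduled measurements.

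**Step 5: which rules are touched.** Fever above 40°C is a trigger with a count of 1. Grade 3 fever is 39.0–40°C. If fever counts as a solicited general event, as its place in Appendix 3 suggests, a grade 3 fever lasting 48 hours or more is also a trigger with a count of 1. The grade 3 local rule uses the centimetre grades. Its count is 1 in the synopsis and 3 in Section 9.1.4, and those two passages must also be reconciled.

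**The case against.** The strongest reply has four parts.

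*The systemic section could mean the whole clinical part of Appendix 3, as opposed to its laboratory tables.* The appendix as a whole is titled as systemic grading scales. The Table 5 row for Appendix 3 carries no restriction and appears to be marked in the telephone column, although the table header is not legible in the text at hand. This is a fair point about ambiguity. However, only one table in the appendix carries the systemic label, and it has no fever row. The wider reading would make fever a call item but would still leave the source of the temperature unstated.

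*A fever would be recorded anyway.* The calls query any adverse event, they decide whether a visit is needed, unscheduled visits are allowed at any time (Table 6), and Section 10.1.1 requires severity and dates for every adverse event. This stands in part: a volunteered fever would leave a record. But it depends on the participant raising it. The Section 10.1.1 severity scale rests on interference with activities, not on degrees. A fever that clears before the visit has no reading to set against 40°C. Footnote m also defines standard collection as events outside the solicited appendices, and fever is inside Appendix 3.

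*Operational supplies may be described elsewhere.* This stands. The protocol refers to several manuals that are not shown. A reader might infer that no thermometer or ruler is supplied, but silence does not establish that. What can be said is that the protocol specifies none.

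*Small errors in size do not matter for halting.* For erythema and induration size, grade 3 begins above 10 cm around a 1 cm patch, so errors of a few millimetres at the 1 and 5 cm cuts affect grading only. This largely stands. The exception is bruising, where grade 3 begins above 5 cm, if Appendix 2 scores count as solicited local events, as Table 5 labels them.

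**Conclusion.** The point holds in a limited form. Read as written, footnote n and the synopsis do not solicit fever on Days 5–7, and Section 3 solicits even less. No method is specified for obtaining temperature or lesion diameter between visits. On nominal days, 4 of the 7 days in the halting window have no scheduled measurement. Fever and the size-based grades are therefore not systematically ascertained on those days.

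The day count assumes nominal visit days and describes opportunity to measure. It does not estimate missed events.

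Two stronger readings are not supported. A reader might infer that fever and local size cannot be measured on Days 5–7, but visits prompted by a call, unscheduled visits and an early Day 8 visit all allow it. A reader might also infer that local severity is biased downwards. Verbal size estimates can err either way, and the protocol gives nothing to fix a direction. Under-capture of fever does follow from the instruction as worded, to an extent that cannot be calculated from the document.

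The change is worth making before enrolment, because it concerns a primary safety endpoint and a single-participant halting trigger.

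**What to change.** 1. Amend Table 5, footnote n, and the Safety Assessments text of the synopsis so that the calls also complete the fever row of Appendix 3.
2. Reconcile these with Section 3, with the promise in the synopsis of contact on every day without a visit (including Day 3), and with the unrestricted Appendix 3 row of Table 5.
3. State how temperature and the diameters of erythema, induration and bruising are obtained between visits. One option is a participant oral thermometer, a ruler and a one-page daily record for Days 1–8, transcribed at each call and checked by the rater at Day 8. If another manual already provides for this, a cross-reference is enough.
4. Reconcile the count for the grade 3 local rule between the synopsis and Section 9.1.4.

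The cost is a text amendment, about 45 inexpensive kits if that option is taken, a small daily burden on participants and some self-measurement error. No dose or halting threshold needs to change for items 1 to 3.
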